#### Existing evidence:

In a systematic review of case management for people experiencing homelessness [30], two CTI studies were identified – one RCT [31] and one historically controlled study [23]. In the RCT, both the CTI and control groups (usual services only) were discharged from an on-site psychiatry program in a shelter to community-based housing in the New York City region. The CTI group reported significantly fewer homeless nights and a decrease in negative psychiatric symptoms. In the historically controlled study, set in eight sites in the US, housing was not provided as part of the CTI. Those receiving CTI spent more days housed, fewer days in institutional settings, lower alcohol/drug use and less psychiatric problems than those receiving usual services.

In a more recent systematic review of case management for people experiencing homelessness or people who are vulnerably housed [19], five CTI RCT studies were identified – one identified in the

[figure not shown]

previous review [31], with the others being set in the Netherlands [32, 33] and the New York region [21, 24, 34]. Of the four RCTs that had housing stability outcomes, one found no significant improvement in outcome for the CTI group [32], two found significant reductions in odds of homelessness [21, 31] and one found higher rates of time spent in housing for the CTI group, but findings converged when CTI services ended [24]. All studies (or in follow-up research) had mental health outcomes; two finding no significant improvement in outcomes [32, 33], one showing a reduction in internalising and externalising behaviours in children under 5 years [24] but no effect on maternal mental health [34], one finding decreases in negative psychiatric symptoms [31] and one finding decreases in psychiatric re-hospitalisation [35]. Only two studies had quality of life as an outcome of interest and both reported no differences between CTI and control group [32, 33].

From our own literature searches using key terms in the aforementioned reviews, and from citation tracking of the key studies above, we found two further CTI RCTs [26, 36], a before and after study [37], a cost-effectiveness study (from a RCT) [38] and a rapid evidence assessment of homelessness services [39]. The effectiveness studies found that those in CTI group had greater continuity of psychiatric outpatient care [36], increased engagement with psychiatric services at six months (but not observed at one year follow-up) [26] and reduced homelessness and psychiatric symptoms [37]. In a cost-effectiveness study from the US, the CTI was found to be cost-effective compared to the status quo for people experiencing homelessness with severe mental illness [38]. The rapid evidence assessment concluded that CTIs were effective services and, more generally, homelessness services that incorporate permanent supported housing elements are effective. The review authors identify RCTs across multiple sites and robust economic evidence (especially in the UK) as gaps in the evidence base.

In summary, there exists some high-quality evidence that CTI improves housing stability outcomes in people experiencing homelessness or groups that are vulnerably housed. The results from the same evidence base on mental health outcomes is not as strong but the majority of studies found CTI achieving favourable outcomes. Only two studies had quality of life as an outcome and only one study, from the UK, was based in a prison. That study [26] did not provide housing as part of CTI, yet provision of suitable accommodation is seen as vital for promoting successful re-integration into the community. In fact, there were only two studies, both from the US [24, 37], that provided housing as part of a CTI intervention. While those two studies suggested the intervention may be effective in improving health, the nature of the housing market and social security support provided in the UK differ markedly and therefore limit generalisability of that evidence.

[figure not shown]

#### 4.1 Rationale for current pilot trial

The adverse health impacts of homelessness are compounded by the experience of imprisonment, with health outcomes substantially worse amongst people with a history of both imprisonment and homelessness than either in isolation [40]. In collaboration with the UK's leading charity for single people experiencing homelessness (Crisis), we will pilot a RCT of a housing-led CTI in four prisons, located in Wales and England. The quantitative and qualitative evidence generated will inform whether a future definitive full-scale trial of the CTI is warranted.

## 5 Trial objectives/endpoints and outcome measures

The overall aim is to conduct a pilot RCT in four male prisons to determine whether a future full-scale RCT assessing effectiveness and cost-effectiveness of a housing-led CTI is warranted. The research questions are:

- 1 **Intervention and randomised trial delivery**
  - 1.1 Is the intervention acceptable to participants, those delivering and those funding?
  - 1.2 What do qualitative and quantitative data suggest in terms of refinements to programme theory, implementation, fidelity, reach, scalability, and acceptability?
  - 1.3 Are there potential harms and unintended consequences of the intervention? How might these be reduced? How can these be measured?
  - 1.4 Are there any potential ethical, practical, statutory, or other legal barriers in running a trial in this population?
- 2 **Recruitment**
  - 2.1 What proportion of eligible people in prison are recruited?
  - 2.2 What proportion of recruited participants are retained?
  - 2.3 What proportion of people in prison provide consent for linkage to routine health and criminal justice data?
- 3 **Data collection procedures**
  - 3.1 Are methods of data collection feasible and what refinements (if any) are needed?
  - 3.2 Are outcome measures suitable and what refinements (if any) are needed?
  - 3.3 What consent and governance requirements are acceptable to data providers for linkage to routine health, welfare, and criminal justice data?
  - 3.4 What are the likely sources of data on the health and broader social impacts of the intervention to inform an economic evaluation in a full-scale trial?

[figure not shown]

### 5.1 Primary outcomes measure(s)

The primary outcome is progression criteria that will determine whether a full-scale RCT of the intervention is warranted. The progression criteria are:

- 1) Recruitment: 50% of those approached agree to participate.
- 2) Retention: 60% of those recruited, in both intervention and control groups, are retained at final follow-up.
- 3) The process evaluation provides evidence that the process is acceptable for participants and staff delivering the intervention.
- 4) The intervention is implemented with fidelity in all settings.

The progression criteria will be agreed in collaboration with an independent Trial Steering Committee (TSC), that will carefully consider progress against these criteria using thresholds for progression according to a traffic light system (green: all criteria are met, the study should progress as designed in this pilot; amber: the majority of criteria are met and with adaptations to methods all criteria could be met; red: the minority of criteria are met and the study should not proceed).

### 5.2 Secondary outcomes measures

Indicative outcome measures for a full-scale trial will be evaluated and will include:

1. **Primary:** Health-related quality of life (SF-12 total score)
2. **Secondary:**
  - Health Related Quality of Life (EQ-5D)
  - Housing stability (i.e., number of days in a stable accommodation)
  - Substance use and hazardous alcohol consumption.
  - Deaths (including cause of death and hospital deaths)
  - Capability wellbeing (ICECAP-A)
3. **Exploratory:**
  - Percentage of participants who consent to link data their data anonymously with routine electronic data through SAIL, NHS England and Ministry of Justice Data Lab.
  - Percentage (of those who consented) of successfully linked records with data held in SAIL, NHS England and Ministry of Justice Data Lab to further inform additional secondary outcomes, for example:
    - Re-incarceration
    - Support networks

[figure not shown]

- Crime (e.g., criminal arrest, criminal convictions, police contacts, rearrest)
- Education training and employment
- Finance, benefits, and debt
- Support network/family & friend connections
- Wellbeing
- Community integration and engagement

## 6 Trial design and setting

This is a multicentre phase 2 pilot Randomised Control Trial (RCT) with an integrated process and economic evaluation. Eighty men leaving prison at risk of homelessness will be recruited and randomised on a 1:1 ratio (stratified by prison) to take part in a CTI or receive usual care. Sites include five male prisons (HMP Liverpool, HMP Altcourse, HMP Risley, HMP Swansea and HMP Parc) where housing-led CTI has recently been introduced and implemented in the first half of 2021. Participants will complete a survey at baseline and followed up at 3-, 6-, 9- and 12-months post randomisation. A subsample of intervention participants ( $n=12$  (x 2 interviews)), control participants ( $n=16$ ), prison staff ( $n=6$ ) and interventionists ( $n=6$ ) will be sampled to maximise variability (based on age, prison, caseworker, differing levels of engagement with the trial (and the intervention specifically), and phases of delivery) to take part in repeated (intervention participants only)/one-off interviews. We will additionally recruit  $n=12$  individuals currently taking part in CTI intervention but not recruited on the trial to take part in a one-to-one interview to find out more about their experiences of the interventions and thoughts on the proposed recruitment methods. Consent will be sought to link with participants routinely collected electronic health records via SAIL and NHS England as well as augmented Criminal Justice data via the Ministry of Justice DataLab.

### 6.1 Risk assessment

A trial Risk Assessment has been completed to identify the potential hazards/risks associated with the trial and to assess the likelihood of those hazards/risks occurring and resulting in harm. This risk assessment will include:

- The known and potential risks and benefits to human participants
- How high the risk is compared to normal standard practice.
- How the risk will be minimised/managed

This trial has been categorised as a low-risk trial, where the level of risk is comparable to the risk of standard care. A copy of the trial risk assessment may be requested from the Trial Manager.

[figure not shown]

## 7 Site and Investigator selection

This trial will be carried out at five male prisons in England and Wales (HMP Liverpool, HMP Altcourse, HMP Risley, HMP Swansea and HMP Parc) where CTI has recently been introduced and is being delivered by CTI workers employed by Crisis (housing charity).

## 8 Participant selection

Participants are eligible for the trial if they meet all of the following inclusion criteria and none of the exclusion criteria apply. All queries about participant eligibility should be directed to the Trial Manager before randomisation/registration. Participants are split between those involved in the RCT and those currently receiving CTI who will only be interviewed/observed.

### 8.1 RCT and non-RCT participants Inclusion criteria

Men leaving prison at risk of homelessness can be included if they are:

1. Aged over 18 years.
2. Released into the Swansea or Liverpool local authority areas and have a local connection (e.g., lived there previously; close relatives living in these areas)
3. Recourse to public funds
4. Have experienced prison and homelessness at least once.
5. Have mental health or substance use support needs.

### 8.2 RCT Exclusion criteria

Men leaving prison cannot take part if they are:

1. under the Multi-Agency Public Protection panel 3 (MAPPA 3)
2. in receipt of Housing First (i.e., support needs too high/complex to benefit from CTI)

## 9. Recruitment, Screening, and Registration

### 9.1 RCT PARTICIPANTS

#### 9.1.1 Participant identification:

Potential participants will be referred to Crisis for eligibility screening by the Community Offender Management Team or Probation service. Crisis will screen potential participants at weekly allocation meetings to see if an individual meets the trial inclusion/exclusion criteria and will invite eligible individuals to take part in the research (using the expression of interest form which provides a summary of the study). Where participants express an interest in taking part, Crisis staff will pass on

[figure not shown]

their details to the research team using an Expression of Interest (Eol) form. Following this, the recruiter (North Westcoast CRN, Swansea Bay University Health Board R&D staff, PHaCT trial team) will arrange access to the prison for the baseline visit with support of the local Crisis CTI staff using the prison visitor scheme.

#### 9.1.2 Screening logs:

will be kept by Crisis CTI staff for each site to record all referrals received regardless of eligibility status and whether they were approached/consented or not. Screening logs will capture non-identifiable information on a tally system relating to referral route, eligibility status, Eol, recruitment status, reasons for non-eligibility or non-recruitment (where possible). Logs will be completed electronically by individually designated Crisis CTI staff for each site. Where there are multiple staff recruiting at one site, entries will be aggregated onto one log. Data entered onto the log will only be accessible to named trial staff members which will be outlined in the Site Delegation Log. Logs will be returned to the Data Manager on a weekly basis using the trial email address.

#### 9.1.3 Recruitment:

A total of 80 participants will be recruited. We will also recruit a sub-sample of intervention participants ( $n=12$  (x 2 interviews)), control participants ( $n=16$ ) prison staff and interventionists ( $n=12$ ) to take part in face-to-face repeated (intervention participants only)/one-off interviews.

#### 9.1.4 Informed consent:

During the baseline visit the potential recruit will be provided with a participant information sheet and trained recruiter will go over the details explaining the risk and benefits of taking part to the potential participant. It will be explained to them that all information they provide, including their personal details, will be kept strictly confidential and will only be accessible to the immediate research team at Cardiff University and that they have the right to withdraw from the study at any time without having to give a reason. Potential participants will be provided with sufficient time to consider their participation and will have multiple opportunities to ask any questions. We might have to share personal data with the University of Glasgow as the Sponsor of this study so that they can check we are following legal processes. This will be managed in strict confidence.

Should they agree to take part, written informed consent will only be obtained by the recruiter (who will be trained in taking informed consent) using the trial Consent Form. A Site Delegation Log will outline who is responsible for taking participants consent and will be kept centrally with the trial team. Participants will be asked to sign two copies (one copy to be kept by the participant and the other to

[figure not shown]

be returned to the TM via registered mail). Only once written informed consent has been obtained from the participant will they be considered a trial participant.

Participants will be asked to provide written consent to take part in a potential qualitative interview, although it will be explained to them that they may not be sampled for this aspect of the trial. It will be further explained that if they later choose not to take part in this aspect of the trial, that this will not impact on their valuable contribution made to the trial so far. They will also be asked if they are willing to consent to trial staff requesting access to their anonymised electronic routine data through a third-party data provider. Participants consent to take part will be verbally reaffirmed at each data collection point.

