## 3. Data entry

[figure not shown]

Within 48 hours of returning to the office, the recruiting staff will be required to enter the data on the bespoke online trial database and the paper CRF and consent form will be sent to CTR via registered mail for review and storage. Once the participants details and CRF responses have been entered the PHaCT trial team will receive an email notification of a new participant entry. This will be monitored by the Data Manager and where an individual has been randomised to the intervention arm, they will then inform the Crisis CTI team of the participants allocation. If recruitment is conducted by a trial team staff member, they will input the data after collection within 48 hours of collection.

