this reason, we will manage and record any safeguarding issues we become aware of during data collection and where possible during intervention delivery. To do this, we will include a safeguarding section in our participant information sheet and data collection forms where we will provide a number of contacts and links where individuals can seek additional support should they require this. Where there are any serious concerns, i.e., risk of harm or death to self or others, these will be reported immediately upon become aware of them to the Chief Investigator and escalated accordingly depending on the nature of the concerns (i.e., calling 999 where relevant or reporting these to the participants probation officers). Consent to escalate these will be collected. To keep a record of any safeguarding concerns, a ‘safeguarding form’ will be completed by the trial team/CRN/R&D staff within 24 hours of becoming aware of the concerns. Reported safeguarding concerns will be reviewed at monthly TMG meetings and signed off by the Chief investigator. Regular debriefing sessions will be held with the recruiters who are involved with data collection to ensure they are well supported. Where any face-to-face data collection will be conducted (i.e., for baseline recruitment, follow-up data collection, interviews or observations) these will take place in suitable public venues and no home data collection will take place. Data collection in the prison will be completed by named recruiter and will follow the visitor system whereby they will be escorted and accompanied by prison staff key holders/Crisis staff.

Safeguarding concerns may include:

- Participants/others safety
- Participants declined mental health
- Research staff safety
- Research staff wellbeing

For any lone working during the qualitative data collection we will follow the guidelines set out in the SOP on lone working (SOP/003/12) to ensure safety of researchers.

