limited for the purposes of a test linkage to records related to periods spent in hospital, use of accident and emergency services, outpatients’ services, and death records [55]. We will request data from 5-years prior to enrolment in the study, to assess the potential of linkage to develop baseline healthcare use estimates, up to the latest data available, to assess the use of linkage to evaluate difference in health outcomes between study arms.

We will also seek to link to criminal justice data via the Ministry of Justice Data Lab (‘the Lab’). The Lab is a service operated by the Ministry of Justice that links details of clients engaging with third sector organisations and provides summary reports of re-offending rates for clients—compared to a matched comparison group that the Lab generates from the wider prisoner population. As the Lab’s services may conflict with trial procedures, such as having two trial study arms and the requirement that summary reports be published on the MoJ website, the test linkage to criminal justice data may not occur if deemed incompatible with study goals.

To link records, personal details will need to be shared with data owners, including name, date of birth, gender, and postcode. It may help data owners if unique identification numbers used by their computer systems are provided; therefore, Police National Computer number and NHS number will also be collected and shared with the appropriate data owner. We will use consent questions and participant information materials based on previous studies from the CTR.

The trial Data Manager will be responsible for the processing of personal data prior to sending it to relevant data owners. Only pre-approved secure methods will be used to transfer personal data between the CTR and data owners. Trial researchers will have access to either aggregated data reports (in the case of the MoJ Data Lab) or de-identified data which will be accessed via a secure gateway (SAIL Gateway)—see data flow diagrams in Appendices.

16 Data Management

A Data Management Plan (DMP) and Qualitative data collection and Analysis Plan (QAP) will be developed to outline the different types of data being collected, collection methods, processing of data, data storage and data sharing. The DMP will include details of the management of the following source data:

|            |             |
|------------|-------------|
| Trial data | Source data |
|------------|-------------|

[figure not shown]

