### 20.2.1 Data sharing

Data will be shared with the University of Glasgow for the purpose of conducting the Health Economic analysis. De-identified data may be made available following review against the CTR policies on data sharing and with an agreed/signed data sharing agreement.

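### Section 9.1.4 has men told that only the Cardiff team sees their data, which the protocol's linkage and data-sharing sections contradict; the linkage-consent rate carries over to a full trial only if the transfer of identifiers is disclosed

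*Protocol*

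**What the plan says.** Section 9.1.4 sets out what the recruiter explains at the baseline visit. All information the man provides, including personal details, "will be kept strictly confidential and will only be accessible to the immediate research team at Cardiff University". Later in the same paragraph comes one exception: "We might have to share personal data with the University of Glasgow as the Sponsor of this study", for the purpose of checking that legal processes are followed. Linkage is put to him as "consent to trial staff requesting access to their anonymised electronic routine data through a third-party data provider". Section 9.1.4 does not mention that identifying details go out in order to make the link.

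Other sections describe wider sharing:

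- Section 15.4 states that "personal details will need to be shared with data owners, including name, date of birth, gender, and postcode", and adds the Police National Computer number and the NHS number. Section 12, item 8, lists name, address, gender, date of birth and, where possible, NHS number, and names NHS England, SAIL and the Ministry of Justice Data Lab as recipients. It limits this to men who consented to linkage.
- Section 20.2.1: "Data will be shared with the University of Glasgow for the purpose of conducting the Health Economic analysis". Section 19 provides for those data to be held at Glasgow for at least 10 years.
- Section 9.1.1 allows recruiters from the Clinical Research Network and the Swansea Bay health board as well as the trial team. Under section 12, item 3, "recruiting staff will be required to enter the data on the bespoke online trial database".

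**The concern.** Two things in the protocol cannot both be true as written: that only the Cardiff team has access, and that direct identifiers go to three outside data owners while a second university receives data for analysis.

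This matters statistically because the pilot measures consent to linkage. It is research question 2.3 in section 5 and an exploratory outcome in section 5.2. Section 15.4 uses the test linkages to judge whether linkage in a full trial would yield a large enough sample. A consent percentage describes the response to a particular request. If men were asked without being told that their names and Police National Computer numbers may go to the Ministry of Justice, the percentage answers a different question from the one a full trial must ask. For men leaving prison, that recipient could plausibly affect the decision.

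**Working it through.** The check is mainly textual. The statement in 9.1.4 is set against each other flow of data.

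1. **Identifiers to data owners (section 12, item 8; section 15.4).** Name, address or postcode, date of birth, gender, NHS number and Police National Computer number leave Cardiff for men who consent to linkage. The sponsor exception in 9.1.4 does not cover this. It contradicts the word *only*. One qualification: section 15.4 says the Ministry of Justice linkage may not take place if it proves incompatible with the study.
2. **Data to Glasgow for economics (sections 19 and 20.2.1).** The exception in 9.1.4 covers Glasgow as sponsor, for compliance checks. Economic analysis is a different purpose, so this also contradicts 9.1.4. Section 20.2.1 does not say that these data carry identifiers.
3. **Recruiters outside Cardiff (section 9.1.1; section 12, item 3).** Network or health-board staff may collect and enter data. This is a literal contradiction but a weaker one, since the man meets the person taking his answers.
4. **The word anonymised.** In 9.1.4 it describes the routine data that trial staff ask to see. Section 15.4 confirms that researchers receive de-identified health data and aggregated Ministry of Justice reports. The description is correct for what comes back and silent on what goes out.

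Precision of the linkage-consent rate: the protocol gives no figure for it, but section 14.3 gives one for a rate in 80 men. The half-width of the 95% confidence interval is 1.96 × √(p(1−p)/n).

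- p = 0.50, n = 80: 1.96 × √(0.25/80) = 10.96 points, matching the stated 11.
- p = 0.75, n = 80: 1.96 × √(0.1875/80) = 9.49 points, matching the stated 9.5.
- Assumed linkage-consent rates, n = 80: 10.74 points at 60%, 8.77 at 80%, 6.57 at 90%.

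These are sampling errors only. The bias from incomplete wording cannot be calculated, because the protocol gives neither an expected linkage-consent rate nor any effect of wording.

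Could a change of wording during recruitment be evaluated? Suppose an even split, 40 men under each wording, and a rate of 50%. Each rate has a half-width of 1.96 × √(0.25/40) = 15.5 points, and the difference 1.96 × √(2 × 0.25/40) = 21.9 points. A formal before-and-after comparison would say little; a descriptive note is all the sample supports.

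**The case against.** The strongest reply is that 9.1.4 summarises a conversation built around an information sheet and a consent form, neither of which is in the document. Section 15.4 says linkage questions and information materials follow earlier studies from the same trials unit, so the transfer may be fully disclosed there. Section 20.2 allows identifying disclosure with specific consent, linkage has its own consent item, and identifiers go out only for men who agree to it. Linkage consent is not among the four progression criteria in section 5.1.

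All of that stands, and it limits the consequence. It does not make the sentence in 9.1.4 true: if the forms are accurate, the protocol has recruiters say something inconsistent with them.

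A reader might infer more, and the documents do not support these further readings:

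- *That the trial breaks a promise and the consent rate is biased.* What men actually read is unknown, so neither is shown.
- *That men disclose risk under a false assurance.* Section 13 does provide for "reporting these to the participants probation officers" among the escalation routes, but it also says consent to escalate will be collected and puts a safeguarding section in the information sheet.
- *That telling Crisis the allocation is a hidden disclosure.* Under section 12, item 2c, the recruiter's script tells the man the next step, including contact from Crisis.
- *That research question 3.3 is compromised.* It asks what data providers will accept, which does not depend on what men are told.

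**Conclusion.** The confidentiality statement in 9.1.4 is contradicted by section 12 item 8 and section 15.4 on identifiers, by sections 19 and 20.2.1 on data for economics, and more weakly by the use of recruiters outside Cardiff. The account of linkage in 9.1.4 is incomplete rather than false. It should be corrected because it governs what men hear before giving a consent that the pilot sets out to measure.

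The effect is confined to research question 2.3 and one exploratory outcome. Its size cannot be stated: sampling error in 80 men is about 7 to 11 points for rates between 90% and 50%, and any bias from wording would be additional and unknown. It could be nil if the unseen forms already disclose the transfer and recruiters follow them.

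**What to change.** Replace the sentence on access in 9.1.4 with the actual recipients and purposes: the recruiting organisations for data collection and entry, Cardiff for running the trial, and Glasgow for both economic analysis and sponsor checks. For men who agree to linkage, name the data owners, state that identifiers are sent to them, and state that de-identified or aggregate data come back. Cross-refer to the consent to escalate in section 13. Make the identifier lists in section 12 item 8 and section 15.4 agree. Then check the recruiter's script, the information sheet and the linkage consent item against the revised text.

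Report the linkage-consent percentage together with the wording used. If the wording changed during recruitment, note that descriptively, with the numbers consented under each wording and no formal comparison.

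The cost is a wording amendment. The observed linkage-consent rate may be lower, but it would be the rate relevant to a full trial.
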